### Sample size

It is planned to recruit 108 women in total.

### Randomisation

Initial random allocation to treatment with rifampicin or UDCA will be in a ratio of 1:1.

Randomisation is managed via a secure web-based randomisation facility hosted on REDCap at The University of Adelaide, with telephone back-up available.

Stratification is by centre and by severity (serum BA concentration prior to randomisation < 100 μmol/L, ≥100 μmol/L).

The woman is allocated a unique participant identification number on randomisation.

### Baseline assessments

Baseline data, including all demography, itch chart results, serum BA concentrations, other serum analytes, viral serology and coagulation profiles, including prothrombin time and activated partial thromboplastin time (recorded within 7 days prior to randomisation, and 4–7 days after cessation of any previously initiated UDCA therapy), are entered on the web-based data base. The itch chart is a previously validated 100 mm visual analogue score where the participant is asked to score her worst itch in the previous 24 h [27]. All laboratory data are measured in the routine hospital laboratories for each centre.

Other biological samples, including serum, urine, faeces, liquor and placenta, may also be collected (with participant consent) under separate protocols and stored for later assessment.

On completion of these details, the database issues a randomisation notification to the site PI/delegate. A prescription for the allocated study treatment is written by the local PI or their delegate, using a standard clinical prescribing script, and the participant collects the study treatment from the pharmacy.

### Subsequent visits

At the first visit a week after randomisation, and then at least monthly, if randomised prior to 28 weeks gestation, and then weekly thereafter, the woman is asked for a value of the worst itch she felt during the previous 24 h, which is then scored on the itch chart. Serum is drawn and monitored for measurement of BA and liver biochemistry and measurement of prothrombin time and activated partial thromboplastin time (as per usual clinical practice), together with any further biological samples for later assessments (with the woman’s consent) under separate protocols, together with routine cardiotocography and ultrasound monitoring (weekly umbilical artery Doppler, 2-weekly growth parameters). The dose of treatment is altered at the discretion of the responsible clinician.

If maximal doses of primary drug therapy are reached, consideration is given to the addition of, first UDCA or rifampicin respectively, following measurement of any appropriate biochemical and microbiological samples, to enable the relevant comparisons to be drawn, and then other therapy, eg cholestyramine, in addition to the trial therapy.

Women in the study, whether randomised to either UDCA or rifampicin, who develop steatorrhoea, are also to be prescribed vitamin K supplements (10 mg daily) to be taken until delivery.

Women may be prescribed pre-delivery antenatal steroids for enhancing lung maturity at the discretion of the treating clinician. Any such antenatal steroid therapy will be recorded in the eCRF.

The remainder of antenatal care and, in particular, decisions about the mode of birth as well as the administration of steroids for promotion of fetal lung maturity, is left to the discretion of the treating clinician. All neonates, and especially those of women taking rifampicin, are to be given parenteral Vitamin K at birth.

The post-delivery outcome will be completed after delivery and before the woman leaves hospital.

Participants will be asked to attend for follow-up at 6 weeks postpartum, with routine blood samples (including BA measurement as well as OGTT, if appropriate) collected 1–3 days beforehand.

### Biological samples and laboratory tests

Routine biochemical, autoimmune and viral serology, and coagulation testing as per local maternity unit guidelines (commonly serum BA, liver biochemistry, including ALT/GGT/bilirubin, viral serology including hepatitis A, B, C, D, E and G (as per local guidelines), cytomegalovirus (CMV), Epstein-Barr virus (EBV) and herpes simplex (HSV), autoimmune liver serology (mitochondrial, smooth muscle, ANA and LKM antibodies) and INR/APTT).

Serum BA do not need to be collected fasting but should be collected shortly before the next scheduled dose of UDCA, if being taken. Fasting/non-fasting and the length of time since the last dose of UDCA should be noted.

### Withdrawal of participants

It will be made clear to participants that they remain free to withdraw from the clinical trial at any time without the need to provide any reason or explanation; and that this decision will not impact on any aspect of their ongoing clinical care. The investigator will be able to discontinue participants from either of the study drugs in the event that they judge that alternative treatment is required, without the woman being necessarily withdrawn from the study. Participants will not be withdrawn for self-reported low or non-adherence to their study treatment.

Permission will be sought to complete and use data up to the point of withdrawal including both:
trial specific datadata collected as per routine clinical practice

Permission will also be sought to ascertain and record subsequent perinatal outcome data.

The reason for withdrawal will be recorded in the eCRF, and, if it was due to an Adverse Event, the investigator will follow up to resolution/stability.

Similarly, it will also be made clear to participants that they remain free to withdraw from any future sub-studies to which they have agreed at any time without the need to provide any reason or explanation; and that such a decision will not impact on any aspect of their ongoing clinical care.

## Statistics

### Rationale for sample size

One hundred eight women are required to have a 90% chance of detecting, as significant at the 5% level, a decrease in maternal pruritus score from -16 mm in the UDCA group to -23 mm in the rifampicin group, (with a standard deviation (SD) of 10 mm across both arms, allowing for a 5% drop out in each arm).

The SD stipulated for the sample size calculation might appear to be too small, on the basis of the values reported in the PITCH study, in which UDCA reduced itching by -16 mm (95% confidence interval -27 mm to -6 mm) [27].. The estimate and 95% Confidence Interval for the difference in pruritus score between the UDCA and the Placebo group was -16 mm (-26.5,  -5.9 mm). This suggests that the standard error is approximately 5.3 mm, and hence the standard deviation of the difference between the groups (given *n* = 55 and *n* = 56) is approximately 28 mm.

The statistical power of the study, however, has been calculated with the intended sample size of 108 (*n* = 54 per group), so as to detect a difference between UDCA and rifampicin if the mean change in pruritus score in the UDCA group is -16 mm (as reported in the PITCH study versus placebo, where change in the placebo group was negligible), while the mean change in pruritus score in the rifampicin group is -30 mm (which has already been stipulated as the minimum change that would be considered clinically meaningful). These calculations were done as the power for a simple comparison of two means, and via simulation to allow for up to five measurements per participant, with correlation between the repeated measures, and show that there is approximately 75% power (with two-sided alpha 0.05) to detect a difference between the groups of this magnitude; i.e., if rifampicin achieves a clinically meaningful reduction in pruritus score while UDCA achieves a reduction of the magnitude reported in PITCH, there is 75% power to detect this.

In the recent PITCHES study, however, the reduction of pruritus score in the UDCA group was much more modest (-5.7 mm) [14]. The CI gives a very similar SD, i.e. 25 mm. This gives much greater power to detect a difference between UDCA and rifampicin: if rifampicin had a change of -23 mm, we have approx. 95% power, and if it had a mean change of -30 mm, > 99% power.

The inclusion of multiple centres will enable maximum recruitment over a limited time scale.

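### The 90% power for a 7 mm difference rests on an SD of 10 mm, which conflicts with the SDs of 25 to 28 mm in the same section; at those SDs power for 7 mm is about 24 to 31%

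*Protocol article*

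**What the plan says.** All statements are in the protocol article, Statistics, Rationale for sample size.

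- **Opening statement.** "One hundred eight women are required to have a 90% chance of detecting, as significant at the 5% level". The mean changes assumed are -16 mm for UDCA and -23 mm for rifampicin, so the target difference is 7 mm. Variability and loss enter the calculation as follows: "with a standard deviation (SD) of 10 mm across both arms, allowing for a 5% drop out in each arm".
- **Doubt about the SD.** The section concedes that 10 mm may look too low. From the PITCH interval for UDCA against placebo it obtains a standard error of about 5.3 mm and, with 55 and 56 women, an SD of about 28 mm. For PITCHES it gives 25 mm.
- **First restatement.** With 54 per group, a UDCA change of -16 mm and a rifampicin change of -30 mm, calculations by a simple comparison of means and by simulation with up to five correlated measurements "show that there is approximately 75% power (with two-sided alpha 0.05) to detect a difference between the groups of this magnitude". The section describes -30 mm as the smallest change regarded as clinically meaningful.
- **Second restatement.** With a UDCA change of -5.7 mm from PITCHES, "if rifampicin had a change of -23 mm, we have approx. 95% power", and more than 99% if the rifampicin change is -30 mm.

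No power is given for 7 mm at an SD of 25 or 28 mm.

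**The concern.** The section carries two incompatible assumptions about variability. The 90% claim uses an SD less than half of either value taken from the two earlier trials, and nothing supports the lower figure. The target of -23 mm also falls short of the -30 mm that the section itself treats as the threshold for a meaningful change.

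What is at stake is how a non-significant result is read. Someone who cites the opening statement would take a null result as good evidence against a 7 mm benefit. At the SDs in the section, a true 7 mm difference would be missed about 69 to 76% of the time.

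**Working it through.** **Inputs.** Two-sided alpha 0.05 (sidedness is stated only for the 75% calculation), 1:1 allocation, 54 per arm, and 54 × 0.95 = 51.3, so about 51 per arm after 5% loss. Differences: 23 - 16 = 7 mm; 30 - 16 = 14 mm; 23 - 5.7 = 17.3 mm; 30 - 5.7 = 24.3 mm.

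**1. The opening statement on its own inputs.**
n per arm = 2 × (1.96 + 1.2816)² × 10² / 7² = 42.9, so 43.
With 5% dropout: 43 / 0.95 = 45.3, so 46 per arm, 92 in total. Inflating the total instead gives 91; a t-based calculation gives 44 per arm, or 47 with dropout. None of these is 108.
Power = Φ(d / (SD × √(2/n)) - 1.96). For d = 7 and SD 10 it is 95% at 54 per arm and 94% at 51. A one-sided test would need only 35 per arm, so sidedness does not explain 108.

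**2. The SD from PITCH.**
SE = (26.5 - 5.9) / 3.92 = 5.26. SD = 5.26 / √(1/55 + 1/56) = 27.7 mm. The stated 28 mm reproduces. The interval behind the 25 mm from PITCHES is not given, so that figure cannot be checked.

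**3. The restated powers at 54 per arm.**

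| Difference | SD | Stated | Recomputed |
|---|---|---|---|
| 14 mm | 28 | about 75% | 73.8% |
| 17.3 mm | 25 | about 95% | 94.9% |
| 24.3 mm | 25 | >99% | 99.9% |

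All three reproduce.

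**4. The figure the section omits: power for 7 mm.**

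| SD | 54 per arm | 51 per arm |
|---|---|---|
| 28 | 25% | 24% |
| 25 | 31% | 29% |

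For example, 7 / (28 × √(2/54)) = 7 / 5.39 = 1.30, and Φ(1.30 - 1.96) = 0.25.

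**5. What 108 women can detect.**
Difference with 90% power = (1.96 + 1.2816) × SD × √(2/n). At SD 28: 17.5 mm (54 per arm) to 18.0 mm (51). At SD 25: 15.6 to 16.0 mm. Conversely, 90% power for 7 mm needs an SD of 7 / (3.2416 × √(2/n)) = 11.2 mm (54 per arm) or 10.9 mm (51).
The expected half-width of the 95% interval is 1.96 × SD × √(2/n), from 9.4 mm (SD 25, 54 per arm) to 10.9 mm (SD 28, 51 per arm). Both exceed 7 mm.

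**6. Could the planned model close the gap?**
The plan's 75% for 14 mm, which it says was also checked by simulation with repeated measures, implies an effective SD of 14 / ((1.96 + 0.6745) × √(2/54)) = 27.6 mm. That is almost the raw 28 mm and gives about 26% power for 7 mm.
Assumed values not in the document, over SD 25 to 28 and 51 to 54 per arm: averaging five measurements with correlation 0.5 to 0.8 gives about 28 to 47%; baseline adjustment with correlation 0.5 to 0.7 gives about 31 to 53%. Only near-zero correlation between repeated measures, or a baseline correlation near 0.9, takes power for 7 mm above 80%. Zero correlation between repeated measures would put power for 14 mm at about 100%, which is not what the plan reports.

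**The case against.** The strongest reply is that the section hides nothing. It raises the SD problem straight after the opening statement, derives the larger value, and restates power for three larger differences, all of which reproduce. By its own threshold of -30 mm the relevant contrast with a -16 mm UDCA change is 14 mm, and about 75% power for that is stated openly. The primary result will be reported with a 95% confidence interval, so a reader can see whether 7 mm is excluded. All of this stands. It limits the fault to an opening statement left unreconciled; it does not supply a reason for 10 mm.

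Three stronger readings are tempting and are not supported:

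- **That the power was miscalculated upwards.** On the stated inputs the opening statement understates power: 108 women at SD 10 give 94 to 95%. The fault is the unsupported SD. The mismatch between 92 and 108 runs in the conservative direction.
- **That this trial's true power is 25 to 30%.** That range belongs to a 7 mm difference, a simple two-mean comparison and SDs borrowed from other trials. PITCHES enrolled ICP of any severity, whereas this trial requires bile acids of at least 40 μmol/L. The Data analysis section plans GEE and baseline adjustment, which could raise power somewhat.
- **That the 95% and >99% figures are also wrong.** A reader might suspect that the -5.7 mm for UDCA is not comparable with an absolute rifampicin change. The document does not give the PITCHES placebo change or say how -5.7 mm was obtained, so no size can be put on this. The figures are right for the inputs stated and should be labelled as conditional on them. Allowing for the 5% dropout moves 95% only to 94%, which is immaterial.

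**Conclusion.** The statement that 108 women are needed for 90% power to detect 7 mm is wrong as written. Its SD of 10 mm is contradicted by the 28 mm and 25 mm in the same section and is nowhere justified, and its inputs lead to about 92 women.

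At the section's own SDs, power for 7 mm is about 24 to 25% (SD 28) or 29 to 31% (SD 25), against the 90% stated. This rests on a two-sided 5% test, 51 to 54 women per arm, a simple comparison of two means, and SDs carried over from the two UDCA trials. The plan's simulation suggests little gain from repeated measures. Baseline adjustment may add something, but under the correlations assumed above power stays at or below about 53%. The conclusion that 90% is not reached for 7 mm is therefore firm; the exact percentage is not.

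**What to change.** Withdraw the 90% / 7 mm / SD 10 statement as the basis for 108. Replace it with text that names the method and the SD, for example:

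> With 108 women (about 102 evaluable after 5% loss), a two-sided 5% comparison of two means has about 71 to 74% power for a difference of 14 mm at SD 28 mm, about 24 to 31% for 7 mm at SD 25 to 28 mm, and 90% power only for about 16 to 18 mm. A non-significant result would not by itself exclude a difference of 7 mm.

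Present the 95% and >99% figures as conditional on a UDCA change of -5.7 mm and an SD of 25 mm. Reconcile the -23 mm target with the -30 mm threshold, so that one difference is clearly the one the trial is sized for. If the sponsor has grounds for an SD near 10 mm, they need to be stated.

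The cost is a rewritten sample-size section with a less favourable stated power. Enrolment, design and analysis do not change.

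### The 75% power figure treats all 54 women per arm as analysed; with the plan's own 5% dropout the simple comparison of two means gives about 71–72%

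*Protocol article*

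**What the plan says.** All the figures are in the protocol article under Statistics, Rationale for sample size, unless noted.

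- The opening sentence gives 108 women for 90% power, "allowing for a 5% drop out in each arm". The separate Sample size section makes 108 the number to be recruited, so the 5% loss falls inside the 108.
- The section then derives, from the earlier placebo-controlled UDCA trial (PITCH), a standard deviation that "is approximately 28 mm".
- Power "has been calculated with the intended sample size of 108", with 54 per group shown in brackets, "if the mean change in pruritus score in the UDCA group is -16 mm" and "while the mean change in pruritus score in the rifampicin group is -30 mm".
- Two methods are named: a simple comparison of two means, and a simulation with up to five correlated scores per woman. One result is given for both: "approximately 75% power (with two-sided alpha 0.05". The same 75% is then repeated as the power that applies "if rifampicin achieves a clinically meaningful reduction in pruritus score while UDCA achieves a reduction of the magnitude reported in PITCH".
- The next paragraph uses the later UDCA trial (PITCHES: change of -5.7 mm, SD 25 mm). It gives about 95% power if rifampicin achieves -23 mm and more than 99% if it achieves -30 mm.

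Dropout is not mentioned in either of the last two calculations.

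**The concern.** The section uses 5% dropout per arm when it justifies the number to recruit, then quotes power as if every recruited woman were analysed. Anyone reading it from the top would assume that the later power figures carry the same allowance.

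The 75% figure matters more than the others. It belongs to the one contrast in which rifampicin reaches the change that the plan calls the minimum clinically meaningful one. It is also the plan's answer to its own admission that the 10 mm SD behind the 90% figure may look too small. It is already well below 90%, so it should be stated on the plan's own dropout assumption.

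**Working it through.** **Inputs (Rationale for sample size).** Two-sided alpha 0.05; difference 30 − 16 = 14 mm; 54 per arm; dropout 5% per arm; PITCH confidence interval -26.5 to -5.9 mm with 55 and 56 women.

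**Step 1: the SD.** SE = (26.5 − 5.9) / (2 × 1.96) = 5.26 mm. SD = 5.26 / √(1/55 + 1/56) = 27.7 mm. The plan rounds the SE to 5.3 and the SD to 28. Both SDs are carried below.

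**Step 2: analysable women.** 54 × 0.95 = 51.3, taken as 51 per arm. Keeping 51.3 adds only about 0.2 to 0.3 points.

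**Step 3: power.** Normal approximation: power = Φ(Δ / (SD × √(2/n)) − 1.96). For Δ = 14 and SD = 28:

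- n = 54: SE = 28 × √(2/54) = 5.39; 14 / 5.39 = 2.60; Φ(0.64) = 73.8%.
- n = 51: SE = 28 × √(2/51) = 5.54; 14 / 5.54 = 2.52; Φ(0.56) = 71.4%.

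The same calculation with the noncentral t distribution, the unrounded SD and the other two scenarios (23 − 5.7 = 17.3 mm; 30 − 5.7 = 24.3 mm):

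| Difference | SD | Printed | 54 per arm (normal / t) | 51 per arm (normal / t) |
|---|---|---|---|---|
| 14 mm | 28 mm | about 75% | 73.8% / 73.1% | 71.4% / 70.6% |
| 14 mm | 27.7 mm | about 75% | 74.8% / 74.0% | 72.4% / 71.5% |
| 17.3 mm | 25 mm | about 95% | 94.9% / 94.6% | 93.8% / 93.3% |
| 24.3 mm | 25 mm | above 99% | 99.9% / 99.9% | 99.8% / 99.8% |

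**Reading the table.** The printed 75% is recovered, to rounding, at 54 per arm. At 51 per arm the simple comparison would need an SD of about 26.8 mm (normal) or 26.6 mm (t) to reach 75%, below anything the section derives from PITCH. Like for like, the loss is 2.4 to 2.5 points (73.8 to 71.4, 73.1 to 70.6, 74.8 to 72.4, 74.0 to 71.5). For the 17.3 mm scenario it is 1.1 to 1.3 points.

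**Step 4: repeated scores, on an assumption.** The correlation used in the simulation is not given, so the simulation cannot be rerun. If five scores share a common correlation ρ, the SD of a woman's mean score is multiplied by √((1 + 4ρ)/5). With SD 28 mm and the normal approximation:

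| Assumed ρ | 54 per arm | 51 per arm |
|---|---|---|
| 0.9 | 77.3% | 74.9% |
| 0.8 | 80.9% | 78.7% |
| 0.7 | 84.6% | 82.5% |

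Losing three women per arm costs 2.1 to 2.4 points here as well, from a starting value that depends on ρ.

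**The case against.** **The figure is right for the n printed beside it.** The 5% is attached to the first calculation (7 mm, SD 10 mm). The later one is a separate check that states 54 per group openly. A reader might infer that the two statements flatly contradict each other; that is too strong. The later figure is an optimistic simplification. What stands is that the section adopts a 5% loss for planning and then leaves it out of the power it quotes, without saying so.

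**A woman who drops out need not contribute nothing.** The itch score is first taken one week after entry and then repeatedly (Trial outcomes; Subsequent visits). The primary analysis is a GEE model (Data analysis). Data up to withdrawal are kept with permission (Withdrawal of participants), and loss to follow-up is expected to be minimal (Dealing with missing data). This stands: 51 per arm is the conservative case, and for the simple comparison the true cost lies between 0 and about 2.5 points. Intention to treat and multiple imputation do not remove the point, because neither restores information from a woman with no follow-up score.

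**The simulation may already cover it.** A reader might infer that the planned primary analysis has only 71% power. The documents do not support that. With an assumed correlation of 0.9 and five scores, 51 per arm would still give about 75%, and lower correlations give more. Equally, the plan reports one approximate figure for both methods and no correlation, so no gain from repeated scores can be credited from the text.

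**The gap is small.** A reader might set 75% against 70.6% and conclude that dropout costs 4 points, or that the chance of missing the effect is 29% and not 25%. That sets a rounded printed figure against the least favourable choices of SD and method. Like for like, the chance of missing it moves from about 25–27% to about 28–29%.

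**Conclusion.** The point holds in a limited form. For the simple comparison of two means named in the plan, the printed 75% is obtained only if nobody is lost. With the plan's own 5% dropout it is about 71–72%. Dropout accounts for about 2.5 points, and the remainder of the gap is rounding of the SD and of the power. The approximate 95% becomes about 93–94%, and the figure above 99% stands.

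This rests on the SD of 27.7 to 28 mm that the plan derives from PITCH, on the 5% falling within the 108 recruited, and on dropouts giving no follow-up score. It says nothing firm about the power of the GEE analysis, whose correlation is not stated. It changes neither the sample size nor the design, and is a minor correction to a stated figure.

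**What to change.** In Rationale for sample size, restate the later power figures at 51 analysable women per arm for the simple comparison of two means: about 71–72% for -16 against -30 mm (SD about 28 mm) and about 93–94% for the 17.3 mm difference (SD 25 mm). The figure above 99% can stay. Add that this is the conservative case in which dropouts provide no follow-up score. Report the simulated repeated-measures power on its own line, with the assumed correlation, the number of scores per woman and the same 5% loss.

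The cost is a sentence or two and one rerun of an existing simulation. The stated power for the simple comparison becomes slightly less favourable. No extra women are needed, and nothing in the design or the analysis changes.

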### Pre-specified subgroup analysis

Pre-specified subgroup analyses will use the statistical test for interaction and where appropriate, results will be presented as differences in means with 95% CIs, and the number needed to treat to benefit or harm calculated. Pre-specified subgroups will be based on:
Serum BA at baseline (< 100 μmol/L, ≥100 μmol/L).Site

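### The sample-size section claims 90% power for -23 versus -16 mm at SD 10, but its own minimum meaningful change is -30 mm and its own SD is 25-28 mm, at which that 7 mm target has about 25-30% power

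*Protocol article*

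**What the plan says.** All the power statements are in the protocol article, Statistics, Rationale for sample size.

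- **Sizing sentence.** It opens "One hundred eight women are required to have a 90% chance of detecting, as significant at the 5% level". The effect to be found is 7 mm: UDCA at -16 mm, rifampicin at -23 mm. The variability it assumes is given as "standard deviation (SD) of 10 mm across both arms, allowing for a 5% drop out in each arm". This is the only sentence that presents 108 as the number required.
- **Second account.** The next paragraph concedes that this SD may look too small and derives about 28 mm from the earlier placebo-controlled pilot trial of UDCA. Power is then given for 54 per group, with UDCA at -16 mm and rifampicin at -30 mm, "which has already been stipulated as the minimum change that would be considered clinically meaningful". The result is "approximately 75% power (with two-sided alpha 0.05"). No other section of the article states the -30 mm threshold.
- **Third account.** Using the later, larger UDCA trial (UDCA -5.7 mm, SD 25 mm), the section says "if rifampicin had a change of -23 mm, we have approx. 95% power", and more than 99% if rifampicin reaches -30 mm.

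Separately, Pre-specified subgroup analysis says "results will be presented as differences in means with 95% CIs, and the number needed to treat to benefit or harm calculated", a promise limited to cases where this is appropriate.

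**The concern.** The sizing sentence aims at a rifampicin change of -23 mm. Two paragraphs later the section treats -30 mm as the smallest change worth having, so by its own wording the sizing target falls 7 mm short. The same paragraphs also replace the SD of 10 mm with one two and a half to nearly three times as large, yet the 90% claim is left standing as the reason for 108 women.

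At stake is what a reader takes the trial's power to be. Someone who stops at the first sentence believes the trial is well powered for a 7 mm difference. If the result is null, that belief would support reading it as evidence against even a modest advantage of rifampicin, which a trial of this size cannot give at the section's own SD.

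**Working it through.** **Inputs**, all from Rationale for sample size: 54 per arm, two-sided alpha 0.05; mean changes of -16 or -5.7 mm on UDCA and -23 or -30 mm on rifampicin; SD 10, 28 or 25 mm. The SD of 25 is taken as stated, because the interval behind it is not printed.

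**SD of 28.** The interval -26.5 to -5.9 mm gives SE = (26.5 - 5.9)/(2 x 1.96) = 5.26 mm. With 55 and 56 women, SD = 5.26/sqrt(1/55 + 1/56) = 27.7 mm. The plan's 28 mm reproduces.

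**Power formula.** Power = Phi(d/(SD x sqrt(2/n)) - 1.96), with sqrt(2/54) = 0.1925. Exact t-based values are in the last column.

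| Scenario | d (mm) | SD (mm) | Plan states | Normal | t-based |
|---|---|---|---|---|---|
| -30 vs -16 | 14 | 28 | about 75% | 73.8% | 73.1% |
| -23 vs -5.7 | 17.3 | 25 | about 95% | 94.9% | 94.6% |
| -30 vs -5.7 | 24.3 | 25 | >99% | 99.9% | 99.9% |
| -23 vs -16 | 7 | 25 | not given | 30.7% | 30.3% |
| -23 vs -16 | 7 | 28 | not given | 25.4% | 25.1% |

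Worked example, last row: 7/(28 x 0.1925) = 1.30; 1.30 - 1.96 = -0.66; Phi(-0.66) = 0.25.

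The three later figures reproduce. The sizing sentence does so only loosely: n = 2 x (1.96 + 1.28)^2 x 10^2/7^2 = 43 per arm (44 by the t method). Dividing by 0.95 gives 46 or 47 per arm, so 92 to 94 in total rather than 108. With 54 per arm and no dropout, power at SD 10 is 95%.

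**Smallest significant difference.** 1.96 x SD x 0.1925 = 9.4 mm at SD 25 and 10.6 mm at SD 28. An observed difference equal to the 7 mm sizing target would not be significant.

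**Could repeated measures rescue SD 10?** The section mentions up to five measurements per woman. For the mean of five with equal correlation rho, the effective SD is SD x sqrt((1 + 4 rho)/5). Even at rho = 0 it is 12.5 mm from 28, or 11.2 mm from 25, still above 10. At rho = 0.9 it is 28 x sqrt(0.92) = 26.9 mm: power is 77% for 14 mm, close to the stated 75%, and for 7 mm it is Phi(7/(26.9 x 0.1925) - 1.96) = 27%. At rho = 0.5 power for 14 mm would be 92%, which does not match the stated 75%. The plan's own 75% therefore implies little gain from repetition.

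**Dropout.** With 5% loss (54 x 0.95, about 51 per arm), power for -30 versus -16 mm at SD 28 is 71%.

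**The case against.** The strongest reply is that the plan has already corrected itself. It admits the SD may look too small, states that power has been calculated at -30 mm, prints the unfavourable 75% openly, and sets -23 and -30 mm side by side in the last scenario. Quoting power at a smaller effect as well is ordinary sensitivity work, and the 95% figure is arithmetically right. All of that stands, so it would be wrong to say that the threshold is ignored in the power rationale. It does not remove the defect: the 90% claim at 7 mm and SD 10 is never withdrawn and remains the stated reason for 108.

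A second reply is that dropping the sizing sentence removes the only derivation of 108 while recruitment is under way, and that 90% power at -30 versus -16 mm with SD 28 would need 85 per arm, or 180 women after 5% dropout. That is true, but the fix below does not re-size the trial. It reports the power that 108 women give.

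A reader might also infer more than the article supports:

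- **That superiority here need not be meaningful.** Any test against zero can be significant below a relevance threshold, and -30 mm is a change in one arm, not a between-arm difference. Targeting -30 mm would not cure this: at a true -30 versus -16 mm with SD 28, about 27% of trials would be significant with an observed rifampicin mean short of -30 mm.
- **That -30 mm is a threshold for the individual woman, so a responder analysis is missing.** The text attaches it to the rifampicin group's mean change. Pruritus was chosen as a continuous outcome, and a responder definition could sit in the separate analysis plan, which is not shown.
- **That a number needed to treat would be built on a cut-off picked from the data.** It is promised only for subgroups and where appropriate, many secondary outcomes are binary, and the analysis plan is to be agreed before analysis. The fault shown is unclear wording.

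**Conclusion.** The section contradicts itself on both the target effect and the SD. Its headline of 90% power for 7 mm falls to about 25-30% at its own SD of 25-28 mm. At its own minimum meaningful change the trial has about 73-75% power if UDCA achieves -16 mm (SD 28) and more than 99% if UDCA achieves -5.7 mm (SD 25). These figures assume 54 analysed per arm, equal SDs and a simple comparison of two means. Baseline adjustment could raise them, but the article gives no correlation from which to judge by how much.

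The primary test remains valid and the other three power figures reproduce. The error lies in the stated justification of the sample size. The subgroup sentence on numbers needed to treat is a minor wording matter: it sits beside differences in means, from which no such number follows without a binary response.

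**What to change.** 1. In Rationale for sample size, reconcile -23 and -30 mm by naming one target effect, and remove the 90% claim based on 7 mm and SD 10.
2. State the power of 108 women at the section's own meaningful change: about 73-75% if UDCA is -16 mm with SD 28, and more than 99% if UDCA is -5.7 mm with SD 25. Keep the 95% for -23 versus -5.7 mm, labelled as a sensitivity scenario.
3. In Pre-specified subgroup analysis, limit the number needed to treat to binary outcomes.

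The cost is rewording and a less favourable headline power. No patients, visits or analyses are added. Because recruitment has begun, the change should be recorded as a correction to the rationale, with the sample size unchanged.
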